### Serious adverse events

The following AEs are classified as serious: AEs resulting in death or posing a life-threatening risk, AEs requiring rehospitalization for treatment or extension of the hospitalization period, AEs leading to persistent or marked disability, and AEs with the potential to cause birth defects in the offspring. AEs will be assessed and graded according to the Common Terminology Criteria for Adverse Events Version 5.0. If a serious AE occurs, the investigators should report it immediately to the principal investigator. If the principal investigator determines a causal relationship between a serious AE and the protocol treatment, a serious AE report will be submitted to the CRB and the hospital director. In addition, information regarding the occurrence of serious AEs will be shared promptly with all the investigators.

### Sample size calculation

The sample size is calculated based on the primary outcome parameter, the R0 resection rate, to assess the non-inferiority of ESMR-L to ESD. These assumptions are based on previous studies and systematic reviews [18–32], with an expected R0 resection rate of 95.2% in the ESD group and 95.3% in the ESMR-L group. The non-inferiority margin is determined following the FDA Non-Inferiority Clinical Trials to Establish Effectiveness Guidance for Industry 2016 (https://www.fda.gov/regulatory-information/search-fda-guidance-documents/non-inferiority-clinical-trials). This FDA guidance illustrates the use of half the difference between the standard treatment and placebo as the non-inferiority margin. According to this guidance, the non-inferiority margin is set at 8% as half the superiority effect of the standard treatment (ESD, 95.2%) over the previous control arm (conventional EMR, the R0 resection rate 78% [29]). Based on these assumptions, 226 participants are required to assess the non-inferiority of the ESMR-L, with a one-sided significance level of 0.05 and a power of 80%. Considering a potential dropout rate of 15%, including patients without NET or NEC in the resected specimen and those who refused consent or were lost to follow-up, 266 patients will be included, with 133 patients in each arm. To achieve sufficient participant enrollment, 32 Japanese institutions will be included in this trial.

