**Methods:**

This is a prospective, open-label, multicenter, non-inferiority, randomized controlled trial of two parallel groups, conducted at the Shizuoka Cancer Center and 31 other institutions in Japan. Patients with a lesion endoscopically diagnosed as a rectal neuroendocrine tumor ≤ 10 mm are eligible for inclusion. A total of 266 patients will be recruited and randomized to undergo either ESD or ESMR-L. The primary endpoint is the rate of en bloc resection with histologically tumor-free margins (R0 resection). Secondary endpoints include en bloc resection rate, procedure time, adverse events, hospitalization days, total devices and agents cost, adverse event rate between groups with and without resection site closure, outcomes between expert and non-expert endoscopists, and factors associated with R0 resection failure. The sample size is determined based on the assumption that the R0 resection rate will be 95.2% in the ESD group and 95.3% in the ESMR-L group, with a non-inferiority margin of 8%. With a one-sided significance level of 0.05 and a power of 80%, 226 participants are required. Assuming a dropout rate of 15%, 266 patients will be included in this study.

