### Statistical analyses

The main analysis will be conducted using the full analysis set (FAS). The FAS is defined as the population of enrolled participants, excluding any of the following criteria: (1) any violation of the inclusion or exclusion criteria, (2) no treatment for the enrolled lesion, (3) no data after randomization, or (4) histologically no NET or NEC after treatment completion. Additionally, a complementary analysis will be conducted using the per-protocol set (PPS), which includes participants from the FAS who have completed the allocated treatment. Adverse events will be assessed in the population of enrolled participants who have undergone the allocated treatment and have been followed up for up to 28 days after the procedure.

The primary assessment parameters, R0 resection rate in each group, and differences between the groups are analyzed. The 90% CI for the difference will be calculated using the Miettinen–Nurminen method. To assess the non-inferiority of ESMR-L, the difference between the groups will be compared to the non-inferiority margin of 8% using a Farrington–Manning test with a one-sided alpha of 0.05. If non-inferiority is demonstrated, the superiority of ESMR-L will be examined using a one-sided alpha of 0.05.

The secondary assessment parameter, en bloc resection rate, will be analyzed using the same method as the primary endpoint. The procedure time, number of hospitalization days, and total cost of the devices and agents are compared using the Wilcoxon rank-sum test. The rates of adverse events between the groups with and without closure of the resection site will be compared using Fisher’s exact test.

A subgroup analysis by expert and non-expert endoscopists will be performed for the primary endpoint, rate of adverse events, and procedure time. Comparison between expert and non-expert endoscopists will be also performed. Factors associated with R0 resection failure will be analyzed using logistic regression.

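### The required sample size of 226 does not follow from the printed assumptions: the trial's named test needs 214, and 226 gives about 82% power

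*Protocol article*

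**What the plan says.** The Sample size calculation section of the protocol article sets the planning rates "with an expected R0 resection rate of 95.2% in the ESD group and 95.3% in the ESMR-L group", and the Methods paragraph of the Abstract repeats them. The same section fixes the margin by reference to the ESD rate: "the non-inferiority margin is set at 8% as half the superiority effect of the standard treatment (ESD, 95.2" per cent) over conventional EMR at 78%. From these inputs it concludes that "226 participants are required to assess the non-inferiority of the ESMR-L, with a one-sided significance level of 0.05 and a power of 80" per cent. A 15% dropout allowance then raises the total to 266, 133 per arm. Randomization is 1:1.

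The Statistical analyses section names the primary test, a comparison with a "non-inferiority margin of 8% using a Farrington–Manning test with a one-sided alpha of 0.05", and for the interval says: "The 90% CI for the difference will be calculated using the Miettinen–Nurminen method". The sample size section does not say which formula or program produced 226.

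**The concern.** The article prints every input that a sample-size calculation for this design needs (two rates, margin, alpha, sidedness, power, allocation), the result, and the test to be used. A reader should be able to get from one to the other, and cannot: the printed inputs and the named test lead to a smaller number.

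What is at stake is the reproducibility of the sample size and power behind the primary non-inferiority claim. The Discussion presents the rigour of the sample-size calculation as a strength over an earlier single-center trial, so the figures should belong to the assumptions printed beside them. Validity, alpha and enrolment are not at stake.

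**Working it through.** **Inputs** (Sample size calculation, Randomization and Statistical analyses sections): p_C = 0.952 (ESD), p_T = 0.953 (ESMR-L), margin Δ = 0.08, one-sided α = 0.05 (z = 1.645), power 80% (z = 0.842), 1:1 allocation, Farrington–Manning test.

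**Formula.** Per arm, n = [1.645·√v0 + 0.842·√v1]² / (p_T − p_C + Δ)². Here v1 = p_T(1 − p_T) + p_C(1 − p_C), and v0 is the same expression at the maximum-likelihood rates restricted to the null, ESMR-L − ESD = −0.08.

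**Printed rates.**
- Restricted rates: ESMR-L 0.8904, ESD 0.9704.
- v0 = 0.8904 × 0.1096 + 0.9704 × 0.0296 = 0.1263.
- v1 = 0.953 × 0.047 + 0.952 × 0.048 = 0.0905.
- Denominator: (0.001 + 0.08)² = 0.081².
- n = 106.96, so 107 per arm, **214** in total. Formula power at 107 per arm is 80.02%.
- After dropout: 214/0.85 = 251.8, so 252.

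**The stated figure.** 226 is 113 per arm, and 226/0.85 = 265.9, so 266: the dropout step is right. The gap is therefore in the 226 itself: 226 − 214 = 12 evaluable patients (12/214 = 5.6%), or 266 − 252 = 14 enrolled.

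**Power of 226 with the printed rates.** 82.1% by the formula, 84.6% by exact binomial enumeration of the Farrington–Manning test.

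**Can another reasonable method reach 226 from the printed inputs?** Totals at one-sided 0.05, 80% power, margin 8 points:

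| Method | Total |
|---|---|
| Farrington–Manning | 214 |
| Miettinen–Nurminen variance factor | 216 |
| Unpooled or pooled normal approximation | 172 |
| Unpooled with continuity correction | 218 |
| Farrington–Manning, null variance only | 240 |
| Blackwelder null variance | 250 |
| Farrington–Manning with continuity correction | 262 |

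None gives 226. Rounding of the rates does not explain it either: over all values that round to 95.2% and 95.3%, Farrington–Manning runs from 104.56 to 109.44 per arm, that is 210 to 220 in total.

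**Changed inputs that do reach 226.**
- Rates exchanged (ESD 95.3%, ESMR-L 95.2%): restricted rates 0.8908 and 0.9708, denominator (−0.001 + 0.08)² = 0.079², n = 112.006, so 113 per arm = 226. Formula power is 79.998% at 112 per arm and 80.3% at 113.
- Printed rates with a margin of 7.75 points: n = 112.88, so 113 per arm = 226.
- Unpooled formula, one-sided 0.025, both rates 95.2%: 2 × 0.952 × 0.048 × (1.960 + 0.842)²/0.08² = 112.1, so 113 per arm = 226.

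The last two contradict what is printed: 7.75 appears nowhere, and one-sided 0.025 is not the stated alpha. The exchange contradicts the printed labels but keeps the stated alpha, power, margin and test.

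**The case against.** The strongest reply is that the article condenses a fuller protocol. Farrington–Manning is named for the analysis, not for planning, and another formula may have been used. That stands as far as the cause goes. It does not rescue the figure, because none of the usual formulas tried gives 226 from the printed inputs.

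The second reply is that the consequence is slight. This also stands. The planning rates differ by 0.1 point, well inside the uncertainty of any such assumption, and the discrepancy adds patients rather than removing them. Even if the rates really are the other way round, 226 gives 80.3% power by formula and 82.9% exact.

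Two stronger readings are tempting, and the document supports neither.

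- A reader might infer that the arms were certainly reversed, since the exchanged rates hit 226 exactly. The match depends on 112.006 being rounded up to 113, other changed inputs also reach 226, and no formula is named. The labels are also consistent: ESD is 95.2% in the Abstract, in the planning assumption and in the margin derivation. A swap is a plausible inference, not a finding.
- A reader might infer that a reversed order would carry into the analysis and put the margin on the wrong side. The article states the direction properly where the test is specified: non-inferiority of ESMR-L to ESD, then superiority of ESMR-L. Planning and analysis are separate runs, and no analysis program is shown.

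**Conclusion.** The point holds as a reproducibility error. Under the named test and the printed assumptions the requirement is 214 evaluable patients (252 enrolled), not 226 (266), and the power of 226 is about 82% by formula or 84.6% exact, not 80%. This rests on reading the printed rates as labelled, 1:1 allocation, and planning by the same test as the analysis. The other formulas tried change the recomputed number but do not produce 226. Reversed entry of the rates fits exactly but is unproven. The discrepancy is conservative, does not underpower the trial and gives no reason to alter enrolment. Confidence is high in the mismatch and only moderate in any explanation of it.

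**What to change.** Keep 266. In the Sample size calculation section, name the formula (and program) used. Then do one of the following:

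- If the printed rates are the intended ones, state that 214 evaluable patients are required and that 226 give about 82% power, and make the Abstract agree.
- If other rates or inputs were used, print those in both places and reconcile them with the margin derivation, which takes ESD as 95.2%. Changing only the planning rates would leave the section contradicting itself.

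As a routine check, confirm in the planning program that the difference is ESMR-L minus ESD and that the null value is −8 points. The cost is a few words and a short look at the program; enrolment, margin and alpha stay as they are.

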### Statistical analyses

The main analysis will be conducted using the full analysis set (FAS). The FAS is defined as the population of enrolled participants, excluding any of the following criteria: (1) any violation of the inclusion or exclusion criteria, (2) no treatment for the enrolled lesion, (3) no data after randomization, or (4) histologically no NET or NEC after treatment completion. Additionally, a complementary analysis will be conducted using the per-protocol set (PPS), which includes participants from the FAS who have completed the allocated treatment. Adverse events will be assessed in the population of enrolled participants who have undergone the allocated treatment and have been followed up for up to 28 days after the procedure.

The primary assessment parameters, R0 resection rate in each group, and differences between the groups are analyzed. The 90% CI for the difference will be calculated using the Miettinen–Nurminen method. To assess the non-inferiority of ESMR-L, the difference between the groups will be compared to the non-inferiority margin of 8% using a Farrington–Manning test with a one-sided alpha of 0.05. If non-inferiority is demonstrated, the superiority of ESMR-L will be examined using a one-sided alpha of 0.05.

The secondary assessment parameter, en bloc resection rate, will be analyzed using the same method as the primary endpoint. The procedure time, number of hospitalization days, and total cost of the devices and agents are compared using the Wilcoxon rank-sum test. The rates of adverse events between the groups with and without closure of the resection site will be compared using Fisher’s exact test.

A subgroup analysis by expert and non-expert endoscopists will be performed for the primary endpoint, rate of adverse events, and procedure time. Comparison between expert and non-expert endoscopists will be also performed. Factors associated with R0 resection failure will be analyzed using logistic regression.

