### Outcome measures

#### The primary endpoint (for non-inferiority)

1. Rate of en bloc resection with histologically tumor-free margins (R0 resection rate)

R0 resection rate is defined as the absence of tumor involvement in both the horizontal and vertical margins, as confirmed histologically in the resected specimen. Evaluation of the horizontal and vertical margins should be performed on the plane where the NET or NEC is present. Margins without NET or NEC, irrespective of the distance, are considered to be tumor-free. Subsequently, R0 resection will be assessed by the operator based on a pathological report.

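### The 8-point non-inferiority margin is carried over to en bloc resection, although it was derived only from R0 rates and has no stated basis for that endpoint

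*Protocol article*

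**What the plan says.** The Statistical analyses section gives the primary analysis of R0 resection in three parts.

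- Interval: "The 90% CI for the difference will be calculated using the Miettinen–Nurminen method".
- Test: "the difference between the groups will be compared to the non-inferiority margin of 8" per cent, "using a Farrington–Manning test with a one-sided alpha of 0.05".
- Follow-on: if non-inferiority is shown, superiority is tested at the same one-sided level.

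The next paragraph applies this to the first secondary endpoint: "The secondary assessment parameter, en bloc resection rate, will be analyzed using the same method as the primary endpoint". It names no other margin, and no other margin for this trial appears in the article.

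The Sample size calculation section explains the margin: "the non-inferiority margin is set at 8% as half the superiority effect of the standard treatment (ESD, 95.2%) over the previous control arm". The comparator figure is given as "conventional EMR, the R0 resection rate 78" per cent. Both rates are R0 rates.

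The primary endpoint is titled "Rate of en bloc resection with histologically tumor-free margins (R0 resection rate"). By that title, an R0 resection is an en bloc resection that also has clear margins.

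**The concern.** A half-effect margin belongs to the endpoint whose effect was halved. Eight points is about half of what ESD gains over conventional EMR in R0 resection. Nothing in the article shows what ESD gains in en bloc resection, so nothing shows that 8 points would preserve half of that gain.

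En bloc rates are also bounded below by R0 rates, so they lie closer to 100% and leave less room for a deficit. A margin sized for R0 may then be generous for en bloc. If the plan is followed as written, the report will carry a formal en bloc non-inferiority verdict, and possibly a superiority verdict. A reader could take it as a second confirmation of the primary result although its threshold was never justified for that endpoint.

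**Working it through.** **Inputs from the article.** Expected R0 rates are 95.2% (ESD) and 95.3% (ESMR-L), and the conventional EMR R0 rate is 78%. The margin is 8 points at one-sided 0.05. There are 226 evaluable participants (113 per arm) and 266 randomized (133 per arm). The Background cites ESMR-L R0 rates of 89–100%.

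**Assumed inputs.** En bloc rates of 95.3% to 100%, because the article gives none.

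**1. The plan's own figures.**
- Margin: (95.2 − 78) / 2 = 8.6 points, set at 8. This reproduces and uses R0 rates only.
- Inflation: 226 / 0.85 = 265.9, so 266. This reproduces.
- Evaluable number: the Farrington–Manning formula with the stated inputs gives 107 per arm (214), not 226. The stated number is on the safe side (exact power for R0 at 113 per arm is 84.6%), and the gap does not bear on this point.

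**2. Largest en bloc deficit for a given R0 rate.** Since R0 is a subset of en bloc, ESMR-L en bloc ≥ ESMR-L R0, and ESD en bloc ≤ 100%. So the maximum deficit is 100 − (ESMR-L R0 rate).
- At the planned 95.3%: 100 − 95.3 = 4.7 points.
- At 92%: 100 − 92 = 8 points, equal to the margin.
- At 89%, the low end cited in the Background: 100 − 89 = 11 points.

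**3. Where the rule changes its answer.** The Farrington–Manning statistic is z = (p_ESMR-L − p_ESD + 0.08) / SE. The SE uses the estimates restricted to a difference of exactly −0.08, and the rule passes if z > 1.645. With no ESD failures in 113, the restricted estimates are 0.92 and 1.00, so SE = √(0.92 × 0.08 / 113) = 0.0255.
- 4 failures against 0: z = (−0.0354 + 0.08) / 0.0255 = 1.75, pass.
- 5 failures against 0: z = (−0.0442 + 0.08) / 0.0255 = 1.40, fail.
- With 133 per arm and no ESD failures, the rule passes up to 5 failures.

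**4. How often the rule passes.** Both binomials were enumerated in full. As a check, the type I error at 95.2% against 87.2% is 4.7% (113 per arm) and 5.1% (133 per arm).

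| Assumed en bloc, ESD / ESMR-L | 113 per arm | 133 per arm |
|---|---|---|
| 99% / 99% | 99.6% | 99.9% |
| 99% / 98% | 94% | 98% |
| 99% / 97% | 80% | 88% |
| 99% / 96% | 60% | 70% |
| 100% / 97% | 75% | 79% |
| 100% / 95.3% | 38% | 40% |

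The last row is the largest deficit compatible with the planned R0 rate.

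**The case against.** The strongest reply is that this shows only a missing rationale for one secondary endpoint, and that the temptation is to claim much more. A reader might infer that the trial's own rates rule out an 8-point en bloc deficit, so that the test carries almost no information or merely repeats the R0 result. The article does not support that reading, for four reasons.

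- The null of any powered non-inferiority test is false under its planning assumptions. At 95.3% against 95.2% the same could be said of the primary R0 test. Planning rates are what the trial examines.
- The 4.7-point bound holds only at 95.3%. The article's own cited range reaches 89%, where the bound is 11 points and exceeds the margin.
- The rule discriminates. It fails at 5 against 0 in 113 per arm, and its pass probability falls to 38% at 100% against 95.3%.
- The two verdicts can diverge. Suppose each arm has 5 R0 failures in 113, all piecemeal under ESMR-L and all positive margins after en bloc removal under ESD. R0 passes (z = 2.44), but en bloc is 5 against 0 and fails (z = 1.40).

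It is also fair that a move from 1% to 3% failures is a tripling in relative terms but only 2 points in absolute terms, and that a risk-difference margin tolerates such gaps by design. The primary method already includes the difference and its 90% interval, which show any deficit whatever the margin. Only R0 is labelled as a non-inferiority endpoint, and the Discussion ties the choice of standard treatment to R0 alone.

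All of this stands and limits the point. It does not supply a basis for 8 points on en bloc. A condensed article may leave detail to the full protocol, but this article does fix the method for en bloc, and the only derivation it offers for the margin concerns another endpoint.

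**Conclusion.** The point holds in a limited form and is minor. On a plain reading the 8-point margin passes to en bloc resection, and its only stated derivation is from R0 rates. At the planning rates it is a lenient threshold, wider than the 4.7-point deficit that a 95.3% R0 rate would allow. A formal pass would therefore add little to the primary result.

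The 4.7-point figure rests on the planned R0 rate being true and on R0 requiring en bloc removal, as the endpoint's title states. The pass probabilities rest on assumed en bloc rates. The sample size, the primary test and the primary conclusion are not affected.

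**What to change.** In the Statistical analyses section, replace the sentence on en bloc resection with wording such as: *For en bloc resection, the number of failures per group and the between-group difference with its Miettinen–Nurminen confidence interval will be reported; no non-inferiority or superiority conclusion will be drawn.*

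If a formal test is wanted, state a separate en bloc margin, derived from the en bloc rates of ESD and conventional EMR by the same half-effect rule, and give the source of those rates. The article does not contain them, so no value can be offered here.

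The first option costs one sentence and the loss of a secondary non-inferiority statement. The second also needs the source rates to be found and justified. Neither changes the sample size, data collection or conduct of the trial.

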### Data registration and management

The investigators will enter anonymized data into a web-based Electronic Data Capture (EDC) system hosted at the Shizuoka Cancer Center. The EDC system and associated databases are secured and protected by passwords. A dedicated data management team (data center) established by the director of the data management office at Shizuoka Cancer Center will be responsible for various data management tasks, including managing the data randomization system, EDC system management, EDC form design, data analysis, and verification. The aggregated data will be stored semi-permanently at the datacenter. When patients request data deletion upon withdrawal of consent, their data will be deleted.

